## Abstract

**Background:**

Psychotherapy is highly effective and widely acknowledged for treating various mental disorders. Nevertheless, in terms of methods for teaching effective psychotherapeutic approaches and competencies, there has been a lack of investigation. Training and supervision are the main strategies for teaching therapist competencies, and standardized role-plays with simulated patients (i.e., trained individuals playing someone with a mental disorder) seem useful for evaluating training approaches. In medical education, this procedure is now internationally established. However, so far, little use has been made of standardized role-playing to evaluate training and supervision in the area of clinical psychology and psychotherapy.

**Methods:**

In this study, standardized role-plays are used to evaluate methods for training and supervision. Central cognitive behavioral approaches for treating depression are taught in the training. The first experiment compares an active training approach (i.e., model learning) with a passive one (i.e., reading manual-based instructions). The second experiment compares a direct supervision technique (i.e., supervision based on video analysis) with an indirect one (i.e., supervision based on verbal reporting). In each experiment, 68 bachelor’s and master’s students of psychology will be randomly assigned to the experimental and control groups. Each student takes part in three role-plays (baseline, post and 3-month follow-up), which are all videotaped. Two independent raters assess therapist competencies in each role-play on the basis of a standardized competence scale.

**Discussion:**

The research project aims to contribute to the development of specific training and supervision methods in order to improve psychotherapy training and patient care.

**Trial registration:**

ISRCTN Registry, ISRCTN19173895. Registered on 10 December 2019.

## Background

Training and supervision of psychotherapists are central to the dissemination of evidence-based psychotherapy [1]. Results on the efficacy of psychotherapy from randomized controlled trials (RCTs) may be integrated adequately into clinical practice only with effective training. To date, psychotherapy has more often been part of research than psychotherapy training; thus, current training approaches cannot be characterized as evidence-based [2, 3].

### Assessment of psychotherapeutic competencies

The appropriate assessment of psychotherapeutic competencies is central to the evaluation of psychotherapy training and clinical supervision methods. Waltz et al. [4] consider therapist competence as the level of skill in treatment delivery, covering relevant contextual variables (e.g., client variables and stage in therapy). For the measurement of competencies, Muse and McManus [5] refer to Miller’s pyramid model [6] and define four levels. At the most basic level of knowledge, measurement may be realized by using multiple-choice questions (MCQs) or essays. For the second level of practical understanding, the former two as well as clinical vignettes and case reports may be used. Assessments of practical understanding may be accomplished via standardized role-plays, and clinical practice assessments via ratings of treatment sessions, supervisory assessments, or patient outcomes. Whereas higher levels of the model are associated more with external validity, lower levels provide more internal validity and opportunities for standardization. Despite their higher external validity, competence assessments within real patient encounters imply a number of difficulties. First of all, competence assessments are dependent on patient difficulty and behavior, and owing to their variability, several measurements are necessary for reliable assessments [7]. By contrast, measuring competence via simulated patients (i.e., at the third level of the pyramid model) reduces the aforementioned problems and facilitates standardization for learning purposes.

### Use of simulated patients

In medical training, the use of standardized role-plays is now widespread [8, 9]. “Simulated patients” are trained persons (laypersons, patients, or actors) portraying a person with a diagnosed disease, whereas “standardized patients” are described as providing their portrayal in a consistent and constant manner [10, 11]. Often, the terms are used interchangeably and are abbreviated as “SP” [9]. In contrast to improvised interactions, SPs are provided with intensive role training in advance of their play, facilitating standardization for training and assessment purposes [11]. Furthermore, SPs may be used for the portrayal of rare clinical situations [12] and to foster experiential learning, modeling, skills training, or learning through feedback [13]. Thus, SPs are commonly used for diagnostics or communication training but also for medical examinations, so-called objective structured clinical examinations [8, 9, 14].

### Simulated patients in clinical psychology

In contrast, within clinical psychology and psychotherapy, the advantages of SPs are not fully exploited and have been recognized only in recent years [15–19]. Although using SPs in clinical psychology is perceived as important for learning, self-efficacy, self-reflection, and therapeutic alliance [15–18], current surveys concentrate on subjective assessments, small samples, or convenience samples or are limited to one-group designs [15–18]. Thus, there is a need for RCTs using SPs in clinical psychology [8].

### Active versus passive strategies

All in all, the evidence indicates that active training strategies (e.g., modeling, feedback, and practical exercises) are more effective than passive ones (e.g., reading manuals) [20]. A meta-analysis by Hill and Lent [21] revealed that training conversational techniques were significantly more effective than no training at all (*d* = 0.89) but that modeling was the most important intervention. But again, most studies were uncontrolled and did not use a training manual, and the meta-analysis did not refer to specific psychotherapeutic interventions (such as cognitive restructuring) but focused on counselling or exploration skills (e.g., showing empathy). Beyond training, competence-based supervision is described as fundamental to the development of psychotherapeutic competencies [22]. Referring to audio or video tapes enables the supervisee to receive specific competence-based feedback, which is considered relevant for skills development [23]. Comparing supervision based on verbal reports (i.e., supervision as usual) with those based on video recordings of therapy sessions, Martino et al. [24] demonstrated that the latter contributed more to competence development. Even so, regarding clinical supervision, only a limited number of systematic and controlled studies have been published to date [12, 25].

### Objectives and hypotheses

Therefore, the aim of this study is to use SPs to evaluate specific training and supervision conditions. Psychology students will be taught distinct interventions relevant for the cognitive behavioral therapy of patients with diagnosed depression (i.e., behavioral activation and cognitive interventions based on an established treatment manual) [26]. The focus on depression was chosen because, on the one hand, it is one of the most prevalent mental disorders [27] and, on the other hand, psychotherapeutic competencies are highly relevant for depression treatment [28, 29].

The study combines the development of SP methods with two consecutive experiments. During the developmental phase, scenarios for the SP portrayals will be developed and validated, instruments for the assessment of therapist behavior and SP authenticity will be developed, SPs will be recruited and trained thoroughly, and their portrayal will be validated on the basis of video recordings.

In the first experiment, two specific training strategies (i.e., reading written instructions with or without modeling) will be compared. In the second experiment, two central supervision techniques (i.e., based on treatment videos versus on verbal reporting) will be evaluated. We expect post-training, psychology students randomly assigned to the active strategy of modeling to display more therapeutic competencies than students who were only reading the written instructions on behavioral activation or cognitive techniques (hypothesis 1). Furthermore, we expect the competence differences between the two groups to persist until the 3-month follow-up (hypothesis 2). Second, we expect that post-supervision, psychology students randomly assigned to supervision based on treatment videos will display more therapeutic competencies than the students who described their treatment verbally to the supervisor (hypothesis 3). Again, we expect the competence differences between the two groups to persist at the 3-month follow-up (hypothesis 4).

## Methods/Design

### Study design

The study is a single-center RCT (see Fig. 1) in which participants (i.e., bachelor’s and master’s students included as either trainees or supervisees) will conduct therapy sessions with SPs. All sessions will be video-recorded. Following a preparation period, both experiments will be conducted consecutively within a 2-year period. Data will be gathered before and after training/supervision and at the 3-month follow-up. Participants fulfilling the inclusion criteria (see below) will be randomly assigned by computer-generated numbers in a 1:1 ratio and allocated to the experimental or control groups and to the order of the training topics (behavioral activation and cognitive strategies or vice versa). The allocation will be implemented by a researcher (who is independent of the role-plays). The researcher will enroll and assign participants and provide sealed envelopes containing the study material. To reduce the possibility for unblinding, the researcher and student assistants will urge all participants not to speak to any other students about the trial.

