### Participants

Participants will be recruited from bachelor’s and master’s psychology courses, mainly at the University of Potsdam. They will be included if they have given verbal and written informed consent to the study researchers and therefore agreed to the video recordings of the standardized role-plays. They will be excluded if they are currently in psychotherapeutic treatment or have insufficient German language skills to participate. Participants can withdraw from the study at any time without any disadvantages arising. According to their preference, students will receive either course credit or an expense allowance of €40. Their retention will be promoted by emphasizing the learning benefits of participation. If a reason for discontinuation or unintended effects is given, it will be recorded and, if required, classified into categories. If any impairments through study participation are perceived, those affected will be offered a dialogue with one of the PIs, who are also licensed psychotherapists.

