### Statistical analysis and power calculation

To avoid attrition bias, we will include all randomly assigned participants in the primary analyses (intention-to-treat). Second, we will perform per-protocol analyses and compare the results with those from the intention-to-treat analyses. We will use chi-squared tests for nominal data and analyses of variance/analyses of covariance (ANOVAs/ANCOVAs) for ordinal and interval data. For the analysis of training/supervision effects, the ANOVAs will involve a group factor (training/supervision condition) and a time factor (before, after, and follow-up). Possible pre-differences between the groups will be taken into account via the ANCOVAs. The α level will be set at 0.05 and Bonferroni-corrected for multiple testing. Missing data will be addressed according to the outcome and data structure (e.g., complete case analyses and imputation by expectation-maximization or by last observation carried forward).

Considering prior studies [24, 52], we assume moderate competence differences between the groups (Cohens *d* = 0.60) and high correlations between competence ratings (*r* = 0.50). Given an *α* of 0.05 and a 1-*β* of 0.80 (power), a sample of 68 participants will be necessary in each experiment, resulting in an overall sample size of 136 (G*Power Version 3.1.9.2) [53].

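### Degree level is named in neither the allocation nor the analysis, and covariate adjustment is tied to possible baseline differences; always adjusting for baseline competence and degree level would be better

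*Protocol article*

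**What the plan says.** All references are to the protocol article.

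- **Participants:** "Participants will be recruited from bachelor’s and master’s psychology courses, mainly at the University of Potsdam". The article does not give the expected share of each level.
- **Study design:** eligible students are "randomly assigned by computer-generated numbers in a 1:1 ratio" and "allocated to the experimental or control groups and to the order of the training topics". Stratification and blocking are neither stated nor excluded.
- **Statistical analysis and power calculation:** "the ANOVAs will involve a group factor (training/supervision condition) and a time factor", the times being before, after and follow-up. The next sentence provides ANCOVAs for possible differences between the groups beforehand and lists no covariates.
- **Same section:** with d = 0.60, r = 0.50, α = 0.05 and power 0.80, "a sample of 68 participants will be necessary in each experiment, resulting in an overall sample size of 136".
- **Abstract:** every student has a baseline role-play, so a baseline value of the primary outcome is planned for everyone.

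**The concern.** The trial mixes two stages of study, and each student's stage is known at enrolment. Stage could plausibly relate both to starting skill and to what a student gains from instruction or supervision. With 34 per arm, the arms can differ in their share of master's students by chance.

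The more concrete weakness is the adjustment rule. As worded, it makes covariates depend on whether differences might be present and does not fix them in advance. Covariates chosen after looking at imbalance leave room for data-driven choice and do not secure the precision that a prognostic covariate gives even when the arms are balanced. The sample size has little slack: planned power is about 0.80, and α is also to be Bonferroni-corrected.

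**Working it through.** **Inputs from the protocol.** N = 68 per experiment (34 per arm at 1:1), d = 0.60, so f = 0.60/2 = 0.30 and f² = 0.09; r = 0.50; α = 0.05 (F test with 1 numerator df).

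**Assumed, because the protocol gives no figure.** Share p of master's students 20–50%; competence gap D between levels 0.3–0.8 within-level SD, equal at baseline and post.

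**1. The plan's own figure.** Between-groups test in a repeated-measures ANOVA with m = 2 ratings: λ = N f² m / (1 + (m − 1) r) = 68 × 0.09 × 2 / 1.5 = 8.16. With df 1 and 66, power is 0.804, and 68 is the smallest even N that reaches 0.80. The stated sample size reproduces.

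**2. What baseline adjustment is worth.**

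- Post score alone: λ = 68 × 0.09 = 6.12, df 1 and 66, power 0.68.
- Change score: variance factor 2(1 − 0.50) = 1, so the same λ and again about 0.68.
- ANCOVA on baseline: residual variance factor 1 − 0.50² = 0.75, λ = 6.12 / 0.75 = 8.16, df 1 and 65, power 0.803.

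For the post-score contrast, the planned 0.80 is therefore reached when baseline is in the model, and not otherwise.

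**3. What degree level adds after baseline.** Let v = p(1 − p)D². With an overall correlation of 0.50, the within-level correlation is 0.5(1 + v) − v = 0.5(1 − v). Residual variance is 0.75(1 + v) without degree level and 1 − 0.25(1 − v)² with it. The proportional reduction simplifies to v/3, so λ = 8.16 / (1 − v/3), df 1 and 64.

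| p | D | v | Reduction v/3 | Power (from 0.803) |
|---|---|---|---|---|
| 0.5 | 0.3 | 0.0225 | 0.75% | 0.806 |
| 0.5 | 0.5 | 0.0625 | 2.1% | 0.811 |
| 0.5 | 0.8 | 0.16 | 5.3% | 0.824 |
| 0.2 | 0.3 | 0.0144 | 0.5% | 0.805 |
| 0.2 | 0.8 | 0.1024 | 3.4% | 0.817 |

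At an even mix the gain is 0.3–2.1 power points. At a 20% share it is about 0.2–1.3.

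**4. Chance imbalance.** The number of master's students in one arm of 34 is hypergeometric. The probability that the arms differ by at least 20 points is:

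| Master's students of 68 | Probability |
|---|---|
| 14 | 0.033 |
| 20 | 0.061 |
| 27 | 0.136 |
| 34 | 0.089 |

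The sequence is not smooth. Twenty points is 6.8 students, and the count difference has the same parity as the total, so an even total needs a gap of 8 and an odd total a gap of 7. Under simple randomisation without fixed arm sizes, simulation at an even mix gives about 0.11.

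**5. Consequence of such an imbalance.** With a baseline slope of 0.5, half the gap remains after adjustment. A 20-point imbalance shifts the estimate by 0.2 × 0.5D / √(1 + v). This is 0.03 SD at D = 0.3 and 0.07–0.08 SD at D = 0.8, against an assumed effect of 0.60.

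**The case against.** The strongest reply is that this rests on silence in a condensed article. Strata, blocks and the covariate list normally sit in the full protocol or the SAP, neither of which is shown. The ANCOVA sentence could cover degree level and could mean that baseline is always included, in which case the gain from baseline is already in hand. The Duration section adds that the taught content is not a standard part of German clinical psychology courses, so both levels may start from a similar point. The sample size reproduces, and no passages contradict each other here.

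Much of this stands, and it rules out several stronger readings that a reader might infer:

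- **That allocation used a single unstratified list.** The text names no strata, but it does not say there are none.
- **That degree level is in no analysis.** It is not named, but the ANCOVAs are open enough to include it.
- **That the levels are known to differ in competence.** No figure is given. A difference is plausible, nothing more.
- **That imbalance would bias the trial.** Randomisation keeps the comparison unbiased in expectation.
- **That degree level would raise power to 0.82–0.84.** That needs a further 5–10% of baseline-adjusted variance. By v/3 at an even mix, v must be 0.15–0.30, so D = √0.60 to √1.20, or about 0.8–1.1 SD. A gap that widened after training would leave more to explain, but the protocol offers no evidence of one.

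What the reply does not remove is the rule the article does state: adjustment is linked to possible group differences and not to a set fixed beforehand.

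**Conclusion.** The point holds as an optional improvement, not as an error. Two levels of training are mixed, degree level is named in neither the allocation nor the analysis, and the adjustment rule is weaker than it need be.

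Degree level alone is a small matter: about 0.3–2 power points beyond baseline competence at an even mix, and a shift of at most about 0.08 SD if a 20-point imbalance occurs. Both rest on an assumed gap of 0.3–0.8 SD, equal at baseline and post, and on an assumed master's share of 20–50%. Unconditional baseline adjustment matters more: about 12 power points for the post-score contrast (0.68 to 0.80), using only the protocol's own d, r and N. That gain is lost only if the primary analysis omits baseline, which the current wording allows.

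**What to change.** 1. Make the primary analysis in both experiments an ANCOVA that always includes baseline competence and degree level (bachelor's or master's) as prespecified covariates, whether or not the groups differ at baseline.
2. State whether allocation is stratified by degree level. If it is not, stratify the allocations not yet made, including all of experiment 2, in permuted blocks within level, with topic order balanced inside the blocks.
3. Vary the block sizes and hide them from the researcher who enrols and assigns participants, so that the next allocation cannot be predicted.

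The cost is one degree of freedom for degree level and slightly more list administration. No extra participants or measurements are needed.

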**Fig. 1 Fig1:**
[figure not shown]
SPIRIT (Standard Protocol Items: Recommendations for Interventional Trials) 2013 figure

In this educational low-risk trial, there is no formal implementation of a trial steering committee, data monitoring committee, or stakeholder group. Nevertheless, the funder decides upon the interim project report upon further funding. The principal investigators (PIs) are responsible for local organization, which is implemented by the researcher and his student assistants (e.g., regarding recruitment and ensuring informed consent). The PIs and the researcher meet weekly to oversee conduct and progress of the trial. Statistical counseling will be provided by another department. At any time, students may consult the university’s ethics review committee and the data security officer if problems or harms arise. The researcher and student assistants will note down reasons for discontinuation as well as any problems that may arise during the trial (e.g., burdens and stress to the participants). During the weekly consultations with the PIs, these problems will be discussed and decisions will be made on how to proceed (e.g., to provide individual support and to stop the trial).

### Participants

Participants will be recruited from bachelor’s and master’s psychology courses, mainly at the University of Potsdam. They will be included if they have given verbal and written informed consent to the study researchers and therefore agreed to the video recordings of the standardized role-plays. They will be excluded if they are currently in psychotherapeutic treatment or have insufficient German language skills to participate. Participants can withdraw from the study at any time without any disadvantages arising. According to their preference, students will receive either course credit or an expense allowance of €40. Their retention will be promoted by emphasizing the learning benefits of participation. If a reason for discontinuation or unintended effects is given, it will be recorded and, if required, classified into categories. If any impairments through study participation are perceived, those affected will be offered a dialogue with one of the PIs, who are also licensed psychotherapists.

### Standardized patients

The SPs will be recruited at the University of Potsdam from courses other than psychology, such as the educational or natural sciences, in order to reduce the probability that participants and SPs know each other. They will be employed as student assistants in order to ensure their engagement, and they will be blinded to the experimental conditions. The authenticity of their portrayals will be validated beforehand by independent external raters.

### Training intervention and comparator

The first experiment pursues the goal of evaluating the role of modeling for developing therapeutic competencies. The interventions are based on an evidence-based manual for the cognitive behavioral treatment of depression [26].

In the experimental group, participants (i.e., student trainees) will watch a video of an experienced psychotherapist who skillfully demonstrates behavioral activation (video 1) and cognitive (video 2) strategies with an SP demonstrating a depressive disorder. Participants will answer two control questions regarding the contents of the videos as a manipulation check. Additionally, participants will receive written instructions on behavioral activation (instruction 1) and cognitive biases (instruction 2).

In the control group, participants will watch two unspecific learning tutorials (i.e., solving a Rubik’s Cube and folding an origami animal) without psychotherapeutic contents, answer two control questions regarding the contents of the videos, and receive the same written instructions as described above.

